# Movement control exercise versus general exercise to reduce disability in patients with low back pain and movement control impairment. A randomised controlled trial

**DOI:** 10.1186/1471-2474-12-207

**Published:** 2011-09-23

## Abstract

**Background:**

Non-specific low back pain (NSLBP) in subacute and chronic stages can be treated effectively with exercise therapy. Research guidelines recommend evaluating different treatments in defined subgroups of patients with NSLBP. A subgroup of patients with movement control impairment (MCI) improved significantly on patient specific function and disability in a previous case series after movement control exercises.

**Methods/Design:**

In a randomised controlled trial (RCT) we will compare the effectiveness of movement control and general exercise in patients with MCI. 106 participants aged 18 - 75 will be recruited in 5 outpatient hospital departments and 7 private practices.

Patients randomly assigned to the movement control exercise group will be instructed to perform exercises according to their MCI. The general exercise group will follow an exercise protocol aimed at improving endurance and flexibility. Patients in both groups will receive 9 - 18 treatments and will be instructed to do additional exercises at home.

The primary outcome is the level of disability assessed using the patient specific functional scale (PSFS) which links the perceived pain to functional situations and is measured before treatment and at 6 and 12 months follow-up. Secondary outcomes concern low back pain related disability (Roland Morris questionnaire, RMQ), graded chronic pain scale (GCPS), range of motion and tactile acuity.

**Discussion:**

To our knowledge this study will be the first to compare two exercise programs for a specific subgroup of patients with NSLBP and MCI. Results of this study will provide insight into the effectiveness of movement control exercise and contribute to our understanding of the mechanisms behind MCI and its relation to NSLBP.

**Trial registration:**

Current Controlled Trials ISRCTN80064281

## Background

Low Back Pain (LBP) is one of the major concerns of current health care [1-5]. Only 10% of LBP cases can be attributed to specific disorders like nerve root compression, vertebral fracture, tumour, infection, inflammatory diseases, spondylolisthesis or spinal stenosis. Consequently, NSLBP, in which the cause of symptoms is unknown, is diagnosed in about 90% of all patients and is a health problem of high economic importance [6].

Patients with NSLBP present diverse clinical findings, courses of disease and prognoses. They therefore make up a heterogeneous group of patients, which may explain why treatment effects in numerous studies looking at specific physiotherapy treatments in the NSLBP group are often discouraging. Identifying defined subgroups of patients within the NSLBP population has been a major focus in recent research [7-12]. Current European guidelines encourage outcome studies in subgroups of patients with a shared diagnostic pattern or prognosis that might benefit from specific treatments [1]. This research agenda is expected to reveal further evidence for the effect of treatments designed for specific subgroups [13]. Of 767 RCTs about the effect of conservative treatment on chronic LBP performed and published between 1982 and 2008, 68 publications examined manual or exercise therapy, of which five studies had an additional subclassification and matched treatments [14].

There is no evidence for the effectiveness of exercise in patients with acute LBP of a less than 6 week duration [1,15-17], but exercise therapy is effective in chronic and subacute LBP [16]. There is evidence that home exercise may be effective in decreasing pain and disability, but results have shown no significant difference between exercise types on work disability [1,18]. There is moderate evidence suggesting that exercise therapy may prevent recurrences of LBP, but there is no evidence for a difference in effect between types of exercise [19]. Individually designed exercise programs are recommended [17] but the question remains as to which types of exercise are effective for which subgroups of patients.

Within the framework of a new NSLBP classification system developed by O'Sullivan, one of the subgroups of patients that can be distinguished contains those suffering from MCI [11]. In a first step, this classification of NSLBP distinguishes between patients with non-mechanical disorders, and patients with mechanical disorders. Whereas in patients with non-mechanical NSLBP, psychosocial factors, fear and catastrophising play central roles, pain in relation to posture and movement is predominant in patients with mechanical NSLBP. Patients with mechanical NSLBP are further divided into those with movement impairment (MI) and movement control impairment (MCI). Patients with MI may suffer movement restrictions in single or multiple directions. MCI is defined as a deficit in the control of movements during functional daily activities. The range of the movement is not restricted in the MCI group.

Clinical tests to identify MCI were developed in recent research [11,20-26]. Further evaluation revealed six tests which reliably detect MCI in patients [27]. (Additional files 1) These tests will be used to select patients with MCI for this study. Movement control tests are easy to perform in clinical practice. Tests and clinical presentation allow a further classification of movement control dysfunctions according to direction in extension, flexion, frontal plane and multi-directional MCIs. (Table 1)

**Table 1 T1:** Five distinct directional patterns of movement control impairment [72] (personal communication)

Direction of movement control impairment	Pain aggravation	Pain relief	Movement control deficit
**Flexion**	Sustained flexion of lumbar spine, e.g. when sitting	Extension of lumbar spine, e.g. when standing and walking	Difficulty controlling lordosis in sitting and flexed positions

**Active Extension**	Sustained extension of lumbar spine	Flexion of lumbar spine, relaxing in flexed posture. Breathing exercises	Difficulty flexing when sitting or breathing with diaphragm

**Passive extension**	Extension of lumbar spine, e.g. when standing or walking slowly	Flexion of lumbar spine, e.g. while sitting	Tilting pelvis posteriorly

**Frontal pain control**	unilateral pain in unilateral loading and sidebending	Control pelvis and thorax in frontal plain	Maintain symmetric posture

**Multidirectional pattern**	Multidirectional	Changing lumbar spine position	Difficulty assuming neutral lordotic spinal positions

Description: Specification of main symptoms and signs to classify the direction of movement control impairment

Two mechanisms are proposed to explain the impaired movement control behaviour. One relates to conditioning and habituation, which are important factors in motor learning. Patients use postures and movements that are potentially harmful due to maladaptive processes, like avoidance or overuse during the acute pain phase [28]. Another mechanism is non-awareness of the posture's pain provocation. Altered cortical representation of the lumbar spine in the presence of pain may play an important role [29]. Two point discrimination is decreased in patients with NSLBP, indicating changes in cortical representation because of NSLBP [30]. Both mechanisms can either be induced by pain or be the cause of pain.

It is hypothesised that, once movement control is impaired, it results in repetitive mechanical deformation of innervated tissue and leads to increased nociceptive input to the central nervous system and, therefore, pain [31]. All joint capsules, ligaments, tendons and muscles are possible pain sources, especially due to continuous strain or longstanding repetitive movements [31,32]. Repeated misuse of these tissues can also initiate the inflammatory cascade, a further cause of pain [33].

The inter-rater reliability of the clinical classification of NSLBP in MI and MCI is very high; in experts and raters with less experience, k = 0.85 and k = 0.6 respectively [34,35]. The inter- and intra-rater reliability of the previously described 6 active tests performed by the patient was evaluated as good to substantial [27]. Validity of MCI tests is supported by significantly different results in healthy subjects, with 0.75 positive MCI tests (95% CI 0.55-0.95) and low back pain patients with 2.21 positive MCI tests (95%CI 1.94-2.48, effect size d = 1.18) [36].

In a preceding prior controlled case series, 38 preselected patients with positive MCI tests were treated with an individualised movement control exercise program and showed improvements in MCI test performance associated with improvements in patient specific functional complaints and disability [37]. The present study will compare movement control training with general exercise in a randomised controlled trial.

MCI exercises are often and falsely referred to as motor control exercises, spinal stabilisation or core stability exercises. While MCI exercises aim to improve function through repetitive normal use, the latter retrain delayed muscle activity first in order to improve control of the spine. Several trials and systematic reviews have evaluated the effect of stabilising exercises with conflicting results [38-42]. A recent randomised placebo-controlled trial with a specific stabilisation program in a population with chronic low back pain found a significant improvement in activity in both the short and long term when measured with a patient specific functional scale (PSFS), and a short term improvement for global impression of recovery and disability [43]. However, they did not subgroup the patients and the effects were not beyond the smallest minimal meaningful clinical change.

The general exercise treatment is based on treatments used in previous studies. Exercises were developed to improve endurance, strength and flexibility of the spinal tissues [44]. Experimental studies have shown that these exercises involve many global and local muscles and improve the stability of the spine [45,46]. In an RCT of patients with subacute and chronic NSLBP, a course of only general exercise was compared with a combination of general exercise and stabilisation exercise. Immediately after treatment, disability was significantly lower in the general exercise group. No differences were found in other outcomes or at follow-up time points [47].

Psychosocial factors have an important impact on treatment outcome in NSLBP patients who also show non-acute [48] depression, pain catastrophising, fear of pain and avoidance. These aspects are part of the fear-avoidance model of chronic pain, and previous data has reported its various effects on treatment outcome [49]. Pain-related fear and subsequent avoidance of movements that patients believe to be harmful can also lead to disability and physical deconditioning [50]. In our study patients with a high risk of psychosocial problems are excluded based on an assessment with the Örebrö Musculoskeletal Pain Questionnaire (ÖMPQ) [51,52]. This influential variable will be observed using the Fear-avoidance beliefs questionnaire.

This randomised controlled trial will, to our knowledge, be the first to compare two exercise programs for a well-defined subgroup of patients with non-specific low back pain and movement control impairment. We will evaluate the effect of individualised movement control exercise versus general exercise on disability during a one year follow-up period.

## Methods/Design

### Design

In this randomised controlled trial we will include patients with non-acute NSLBP and MCI. Patients will be recruited and treated in 5 hospital outpatient departments and 8 private practices in Switzerland. Movement control exercise will be compared to general exercise. Treatment outcomes are to be measured at baseline, post-treatment, and at 6 and 12 months follow-up (Figure 1).

**Figure 1 F1:**
[figure not shown]
**Flow-chart of research design**.

Ethical approval has been granted by the Swiss Ethics Commission for Clinical Trials in the cantons of Zurich, Basel and Aargau (Switzerland). Reporting of the RCT will follow the recommendations of CONSORT Statement 2010 http://www.consort-statement.org
 [53].

### Hypotheses

1. In NSLBP patients with MCI, treatment with movement control exercises will result in a significant decrease in disability compared to general exercise, measured with the patient specific functional scale.

2. In NSLBP patients with MCI, improvement in motor control of the lumbar spine, assessed with standardised clinical tests, is associated with functional improvement and pain reduction.

### Participants and recruitment

Admission criteria for the study are described in Table 2. Eligible are patients with NSLBP referred to physiotherapy by their physician. Patients will be recruited by the participating physiotherapists. Patients are included in the study if at least 2 MCI tests are positive and if they present clinical symptoms of MCI as described by [21,24,25,27,30,36]. Patients with specific LBP, identified by the physician or by the physiotherapist are excluded from the study. To prevent floor effects in outcome measurement, a minimal disability of 5 points on the Roland and Morris Disability Questionnaire (RMQ) [54] is required. Excluded are patients with predominant psychosocial factors, defined as a score of more than 130 points on the Örebrö Musculoskeletal Pain Questionnaire (ÖMPQ) [51,52]. An ÖMPQ score of over 130 has been shown to correctly predict failure of return to work in 86% of cases [51]. The German version of the ÖMPQ has been used in a previous study in Switzerland [55].

**Table 2 T2:** Inclusion and exclusion criteria

Inclusion criteria	- Age 18 to 75 years - Non-acute LBP (> 6 weeks duration of symptoms) and less than 3 months of sick leave due to LBP - Two or more positive tests for impaired movement control (Luomajoki et al 2007) - At least 5 points on Roland Morris Disability questionnaire [54] - Clinical behaviour: posture and movement aggravate and ease symptoms; symptoms are relieved by reducing the strain on the lumbar region - Written informed consent
Exclusion criteria	- Specific LBP (Fractures, carcinoma, anomalies, nerve root affection with neurological signs e.g. sensitivity or reflex loss, muscle weakness, radicular pain below the knee) - Less than 6 weeks post-surgery following all surgery on the lower back - post-surgery with spondylodesis - high level of psychosocial risk factors (> 130 points on the ÖMPQ) - Peripheral or central neurological disease - Contraindications for exercise, e.g. major cardiovascular disease or postural hypotension - Inability to understand the purpose of the study - Psychological or psychiatric problems - Chronic abuse of toxic substances such as drugs or alcohol - Use of neuroleptics, sedatives, anti-epileptics and antidepressants

### Baseline assessment and randomisation

After eligibility has been confirmed, patients will be informed about the study comparing two treatments that are widely used in physiotherapy. After obtaining written informed consent, baseline measurements will be performed (see next paragraph). Participants will then be randomised using block allocation with a block size of four, to receive either movement control or general exercise. Randomisation is concealed and performed by an independent assistant at the School of Health Professions at the Zurich University of Applied Sciences via telephone.

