### Sample size calculation

Based on the results of our previous case series, inter-group difference in improvement of 0.9 points on the PSFS is to be used [71]. This difference is also clinically relevant as it displays an improvement of approximately 20% compared with an expected PSFS baseline score of 5 points. We used a standard deviation of 1.5 points, alpha was set at 0.05 and the power was set at 0.9. In each group, 48 patients are needed. Anticipating a 10% drop-out rate, the required sample size was set at 106 patients to be randomised.

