### Blinding

Patients and therapists cannot be blinded to treatment. To keep patients unaware of any expected treatment group benefit, patients will be informed that the effect of two well-established therapies is to be evaluated. An independent and blinded assessor will record videos of the movement control tests at the end of the treatment phase and perform the post-treatment physical examination. A second blinded assessor will rate the video recordings of the MCI tests. Statistical analysis will be blinded regarding treatment group code. The researcher who will perform the statistical analyses will not be involved in taking the measurements.

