## Discussion

This randomised controlled trial will compare the effectiveness of two exercise-based physiotherapy treatment protocols in a well-defined subgroup of NSLP. Inclusion is based on the clinical diagnosis of MCI with clinical tests shown to be reliable. The MCI tests allow easily applicable selection of participants. We will evaluate whether a treatment protocol addressing movement control problems is more beneficial than a general exercise protocol.

The multicentre design of the study allows treatment by different physiotherapists and improves generalisability. The selection of patients reflects the population usually found in different clinical settings. Randomisation is organised centrally and prevents selection bias.

Both treatment protocols are widely used and well-established in physiotherapy. The physiotherapists treating each group are equally instructed and experienced in applying the respective treatments. This prevents a disadvantage for the participating patients regarding group allocation.

Blinding the therapists is generally not possible. To minimise measurement bias, the measurements taken after the treatment will be taken by an assessor not involved in the treatment procedures.

The results of this study will provide evidence to improve the selection of exercise treatments for patients with NSLBP and MCI. Results will also contribute to the understanding of the mechanisms behind MCI and its relation to low back pain.

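### One fixed, published block size of four with unblinded recruiting physiotherapists makes the claim that central randomisation prevents selection bias too strong; how predictable allocations are depends on the blocking level

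*Protocol article*

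**What the plan says.** Under Baseline assessment and randomisation, the Protocol article gives a single block size: "Participants will then be randomised using block allocation with a block size of four". The same section describes the safeguards. "Randomisation is concealed and performed by an independent assistant", by telephone, and the call comes late in the sequence: "After obtaining written informed consent, baseline measurements will be performed", and only then is the patient allocated.

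Under Participants and recruitment: "Patients will be recruited by the participating physiotherapists". Several eligibility criteria are thresholds (number of positive movement control tests, RMQ score, ÖMPQ score), but some need judgement. The patient must show clinical symptoms of movement control impairment, and "Patients with specific LBP, identified by the physician or by the physiotherapist are excluded from the study".

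Under Blinding: "Patients and therapists cannot be blinded to treatment".

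The Discussion concludes without qualification: "Randomisation is organised centrally and prevents selection bias".

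The article is dated 23 September 2011. Its Results section expects inclusion to run from July 2010 to the end of 2011. The abstract counts 12 sites (5 + 7) and the Design section 13 (5 + 8). The article does not say whether blocks run within site or along one list for all sites.

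**The concern.** Concealing the next assignment and preventing its inference from past assignments are separate protections. An independent telephone service gives the first. The second depends on whether someone at the site can tally earlier allocations and knows, or can work out, where a block ends. Here the block length never varies, it was made public while patients were still to be enrolled, and the people who recruit work where treatment is given unblinded.

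A recruiter who anticipates the next arm does not need to break the telephone procedure. The influence comes earlier: whom to approach, when to enrol, how to read a borderline clinical sign. Consent and baseline measurement before the call prevent exclusion once the arm is revealed, but not this. The primary outcome, the PSFS, is self-reported by patients who know their treatment, so the comparison relies heavily on sound allocation.

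**Working it through.** The plan gives no predictability figure to reproduce, so the check starts from its stated design.

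**Inputs.** Block size 4 (Baseline assessment and randomisation). Two arms, with 1:1 allocation implied by "In each group, 48 patients are needed" (Sample size calculation). 106 patients to be randomised. 12 or 13 sites.

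**Case A: the recruiter sees every allocation in the block** (blocks within site, or shared knowledge). There are six equally likely orderings of AABB. The recruiter guesses the arm with more places left.

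| Position in block | Probability of a correct guess | Probability that the allocation is certain |
|---|---|---|
| 1 | 1/2 | 0 |
| 2 | 2/3 | 0 |
| 3 | 1/3 × 1 + 2/3 × 1/2 = 2/3 | 1/3 |
| 4 | 1 | 1 |

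- Correct guesses: (0.5 + 0.667 + 0.667 + 1)/4 = 2.833/4 = 70.8%.
- Certain allocations: (1/3 + 1)/4 = 33.3%, or 106/3 ≈ 35 of 106 patients.

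**Case B: one list for all sites, own-site knowledge only.** Simulated with 106 patients falling at random on equal-sized sites. The recruiter guesses the opposite of the last allocation seen at the same site.

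| Sites | Correct guesses |
|---|---|
| 2 | 58.8% |
| 5 | 54.5% |
| 12 | 52.2% |
| 13 | 52.0% |

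Chance is 50%. Guessing from the running own-site tally instead gives about 51% with 12 or 13 sites. Unequal recruitment, with a few dominant sites, would move the result towards the upper rows.

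**When publication could matter.** From 23 September to the end of 2011 is about 3 months of an 18-month inclusion period. Under even accrual (an assumption) that is 106 × 3/18 ≈ 18 patients. Whether recruiters knew the block size earlier is not stated.

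**What varying the block size gains.** The recruiter is assumed to see the whole list.

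| Scheme | Certain allocations | Correct guesses |
|---|---|---|
| Fixed 4 | 33% | 71% |
| Random 4 or 6, undisclosed | about 6% | about 69% |
| Random 4, 6 or 8, undisclosed | about 2% | about 68% |

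The mixed rows are simulated for a recruiter who knows which sizes are possible but not which is in use. The hit rate moves little because the arms return to balance at the end of every block, whatever its length. Adding blocks of 2 gains almost nothing on this measure: expected correct guesses are 1.5 of 2, 2.833 of 4 and 4.1 of 6, so an equal mix gives 8.433/12 = 70.3%.

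**The case against.** The strongest defence is that nothing in the article places blocks within site. One independent assistant randomises by telephone and no stratification by centre is mentioned. The natural reading may be a single list, under which guessing is close to chance. The blocking level is also a detail that a condensed article can leave to the full protocol. This stands, and it makes the predictability conditional. It does not rescue the Discussion sentence, which credits central organisation alone with preventing selection bias.

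The defence can add that most eligibility criteria are thresholds, that a recruiter need not treat each patient recruited, and that no text says recruiters keep a tally. These points lower the likelihood of harm but do not remove the route.

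Three stronger readings are tempting, and the document supports none of them:

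- **That allocations were in fact guessed.** This needs within-site blocks or shared knowledge, and the article states neither.
- **That any resulting bias could be neither detected nor removed.** Data analysis plans baseline comparisons and a multivariable regression on baseline differences. These address measured factors such as baseline disability, fear-avoidance and age. Only selection on unmeasured factors, such as motivation, escapes.
- **That a single list fails too, because arms are then not balanced within centre.** Lack of balance within centre is not selection bias and does not contradict the Discussion.

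**Conclusion.** The point holds in conditional form and is a minor improvement, not a flaw that undermines the trial. A constant block size of four, disclosed while unblinded site physiotherapists were still due to recruit, leaves a route for inference that telephone concealment does not close. The route ranges from substantial (one third of allocations certain, 71% guessable) to nearly negligible (about 52% guessable), depending on a blocking level that the article does not state. The upper figure assumes a recruiter who tracks every allocation and knows the block size. The lower assumes equal sites and no exchange between them. Because the stated safeguards do not exclude the upper case, the unqualified claim of prevention should be softened.

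**What to change.** For patients not yet randomised:

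1. Have the central telephone office use randomly varying block sizes, for example 4, 6 and 8, and do not disclose them to the sites.
2. Keep the existing blocking level. Do not add stratification by centre for this purpose: if the trial now uses one list, stratifying would raise a site recruiter's hit rate from about 52% to around 70%.
3. Reword the Discussion sentence to say that central randomisation *reduces the risk of selection bias*.

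The cost is a new computer-generated list at an office that already exists, and slightly looser arm balance. An unfinished block can leave the arms apart by up to half its length, so by 4 patients with a block of 8 against 2 with a block of 4. The benefit is mainly fewer certain allocations, and it reaches only the remaining patients. The rewording costs nothing and is warranted whichever blocking level applies.
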